### Study hypotheses

The principal hypothesis of this study is that ketamine IM provides similar efficacy to active treatment in patients with TRD due to a comparison between the experimental intervention (ketamine IM) vs. active treatment (escitalopram and aripiprazole). Other objectives of the study include confirming the safety and tolerability of the use of ketamine IM during acute and maintenance treatment.

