### Sample size calculation

The sample size was calculated based on a similarly designed RCT (45). Assuming a statistical power of 90% with a clinically significant minimum effect of 0.5 (Cohen's d) and alpha 5%, a total of 88 subjects will be needed (44 in the EG and 44 in the CG). Given this is a long-duration study, a drop-out rate of 10–20% was estimated.

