### Statistical analysis

All analyzes will be performed using the Statistical Package for the Social Sciences-SPSS® (82). Specific and sociodemographic variables will be expressed generally and between intervention groups in relative and absolute frequencies, means, medians, standard deviation, and 95% confidence interval. Continuous variables will be evaluated by the *T*-student or U-Mann Whitney-test according to their distribution and the qualitative ones by the *X*^2^-test. The distribution of variables will be evaluated using the Shapiro Wilk. The global significance level adopted is 0.05. To determine the effects of intervention throughout the study (main outcome and other scales), repeated measures ANOVA (two-way) will be applied, considering the temporal effect of visits (v-0 to v-final) and the intervention effect (EG × CG). In identifying the significant interaction effect, one-way repeated measures ANOVA test or its non-parametric alternative (Friedmann test) will be performed to verify that the effect is independent of treatment. Contingency tables and *X*^2^-tests will be applied to compare responders and non-responders in the intervention groups. Analysis using intent-to-treat (ITT) will be employed to assess the results (83). Vital signs will be assessed using two repeated measures ANOVA (two-way). First, considering the effect of the intervention immediately (3 evaluations at each visit) and the second, evaluating the effect of the intervention on VS over time (acute and maintenance treatment).

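### The principal hypothesis is similar efficacy, but the trial is sized and analysed to find a difference, so no planned result can establish it

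*Protocol article*

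**What the plan says.** Three parts of the Methods in the protocol article bear on this.

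- **Study hypotheses:** "The principal hypothesis of this study is that ketamine IM provides similar efficacy to active treatment in patients with TRD". This is a similarity claim against escitalopram and aripiprazole.
- **Sample size calculation:** the trial is sized for "a clinically significant minimum effect of 0.5 (Cohen's d") at 5% alpha and 90% power, and concludes that "a total of 88 subjects will be needed (44 in the EG and 44 in the CG"). The calculation is said to rest on a similarly designed trial, which the Introduction describes as placebo-controlled. The 0.5 is an effect to be detected, not a margin to be excluded.
- **Statistical analysis:** for the main outcome and the other scales, "repeated measures ANOVA (two-way) will be applied, considering the temporal effect of visits (v-0 to v-final) and the intervention effect". Responders are compared by chi-square test. "The global significance level adopted is 0.05". The only confidence intervals mentioned are descriptive summaries of specific and sociodemographic variables.

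The article gives no equivalence or non-inferiority margin and no rule for judging the group difference by its confidence interval. It does not say how a non-significant result will be interpreted.

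**The concern.** A test of difference takes equality as its null hypothesis. It can give evidence against equality, but failing to reject is not evidence for it. Here the principal hypothesis lies on the null side of the only planned tests. Rejection would contradict it, and non-rejection would leave it undecided.

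The incentives also run the wrong way. Anything that adds noise or removes information makes non-significance more likely, and that is the only planned result that looks compatible with the hypothesis. A regimen that is worse by an amount the article itself calls clinically significant could then be described as similar to active treatment. The trial's main conclusion is at stake.

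**Working it through.** **1. The statements side by side**

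| Element | What the article fixes | Type of claim |
|---|---|---|
| Principal hypothesis | Ketamine IM has similar efficacy to active treatment | Similarity |
| Sizing | Detect d = 0.5, alpha 5%, 90% power, 44 per arm | Difference |
| Main analysis | Two-way repeated measures ANOVA at 0.05 | Difference |
| Responders | Chi-square test | Difference |
| Margin or interval rule for the group difference | None stated | – |

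The hypothesis does not fit the other stated elements. This needs no arithmetic and does not depend on the sample size.

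**2. The plan's own figure**

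The 44 per arm is taken as given. It does not reproduce as a simple two-sample calculation: d = 0.5, two-sided 5% and 90% power give 85 per arm. That is a separate point, and nothing here rests on it.

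**3. How often a difference of 0.5 SD would be missed**

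Inputs from the article: 44 per arm, a difference of 0.5 SD and alpha 5%. The MADRS schedule is 3 × 4 = 12 assessments in the acute phase, 24 weekly in maintenance and 4 weekly after treatment, about 40 in all.

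Assumptions, not in the article: a two-sided test, all 44 per arm contributing, SD 1 at each visit, the same 0.5 SD difference at every visit, and compound symmetry with correlation ρ.

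The variance of a patient's mean over m visits is V = (1 + (m − 1)ρ)/m.

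- One value per patient: V = 1.
- m = 40, ρ = 0.7: V = (1 + 27.3)/40 = 0.7075.
- m = 40, ρ = 0.5: V = (1 + 19.5)/40 = 0.5125.

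The standard error of the difference is SE = √(2V/44). The 95% interval half-width is t(0.975; 86 df) × SE = 1.988 × SE. The chance of non-significance comes from the noncentral t distribution with noncentrality 0.5/SE.

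| Case | SE | Half-width (SD) | 0.5/SE | Chance of non-significance |
|---|---|---|---|---|
| One value per patient | 0.213 | 0.42 | 2.35 | 36% |
| 40 visits, ρ = 0.7 | 0.179 | 0.36 | 2.79 | 21% |
| 40 visits, ρ = 0.5 | 0.153 | 0.30 | 3.28 | 10% |

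The normal approximation Φ(1.96 − 0.5/SE) gives 35%, 20% and 9%, in agreement.

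**4. What a non-significant interval would show**

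The result is non-significant when the estimate is closer to zero than the half-width. The interval excludes 0.5 SD in both directions only when the estimate is closer to zero than 0.5 minus the half-width: 0.08, 0.14 or 0.20 SD in the three cases. Estimates from there up to 0.42, 0.36 or 0.30 SD are non-significant, yet their intervals still contain a difference the article calls clinically significant.

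**5. If a similarity claim were tested properly**

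No margin is stated, so 0.5 SD is assumed. On the article's own terms a margin could hardly be larger. With a true difference of zero, power is Φ(0.5/SE − 1.96) for non-inferiority (one-sided 2.5%) and 2Φ(0.5/SE − 1.645) − 1 for equivalence (two one-sided 5% tests).

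| Case | Non-inferiority | Equivalence |
|---|---|---|
| One value per patient | 65% | 52% |
| 40 visits, ρ = 0.7 | 80% | 75% |
| 40 visits, ρ = 0.5 | 91% | 90% |

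A smaller margin lowers every entry.

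**The case against.** **The misreading is not written down.** A reader might infer that the trial will declare similarity whenever p > 0.05. The article does not say so. It is silent on how a non-significant result will be read, and its wording about confirming something concerns safety and tolerability only. This objection stands: the misreading is possible but not planned. The planned tests still cannot establish the hypothesis.

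**The power argument is separate.** A reader might also fold in the claim that the trial is underpowered. Whether 88 patients give 90% power at d = 0.5 belongs to the sample size section. The mismatch would be the same in a trial of any size, so it should not be argued from that.

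**The single-measurement figure is not the planned analysis.** The article names repeated measures ANOVA and intention-to-treat. The 36% figure therefore belongs at the unfavourable end of a range, and it cannot be adjusted for drop-out without assuming how missing values are handled. This also stands. If the visit-by-treatment interaction is the target rather than the average difference, none of the figures applies directly.

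**The wording may be loose, or a margin may exist elsewhere.** The article otherwise calls the trial comparative and never says equivalence or non-inferiority. Similar efficacy may be an expectation rather than a formal hypothesis, and a fuller protocol or analysis plan could hold a margin. The absence of a margin alone would not be a finding. But the article itself states the hypothesis, the sizing and the tests, and these do not agree. If the wording is merely loose, rewording the hypothesis resolves the point.

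**Conclusion.** The point holds as a contradiction within the article: a similarity hypothesis, a sample size aimed at detecting a difference, and only tests of difference. No planned result can establish the principal hypothesis, and a non-significant one could be misread as doing so.

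The size of that risk can only be given as a range. With 44 per arm and a true difference of 0.5 SD, the chance of a non-significant result runs from about 10% to about 36%. The lower figure assumes 40 averaged visits with correlation 0.5, the upper one value per patient. The half-widths run from 0.30 to 0.42 SD. These rest on compound symmetry, a constant effect, a two-sided test and no loss of patients, none of which the article states. The contradiction itself rests on none of them.

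**What to change.** Restate the principal hypothesis as a hypothesis of difference, in line with the sample size and statistical analysis sections. Add that the conclusion will rest on the difference in MADRS between the experimental and control groups with its 95% confidence interval, and that p > 0.05 will not be reported as similar efficacy.

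If the similarity claim is to stay, fix a justified margin on the MADRS difference before unblinding, judge the confidence interval against it in place of the ANOVA decision, and state the power that 44 per arm gives for that claim.

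The cost is more than editorial. The article says the study is running, so rewording the principal objective needs an amendment, and it must precede unblinding to be credible. The sponsor also gives up any similarity conclusion drawn from a null test. The margin route adds the work of justifying the margin, and the stated power may prove too low for the claim.

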### Measures and outcome variables

The study will assess (given in Table 1):

Sociodemographic variables: gender, marital status, ethnicity, number of children, income, education, and employment.Clinical characteristics over the life course: clinical and psychiatric comorbidities, smoking, family history of mood disorders, prior pharmacological treatment and ECT, number of mood episodes, previous psychiatric admissions, suicide attempts, currently receiving psychotherapy, and history of sexual, or physical abuse.Clinical history: visits to the emergency room, attempted suicides, or psychiatric hospitalizations.The Montgomery-Åsberg Depression Rating Scale (MADRS) (70, 71): will be applied as a primary outcome measure 3× per week for the first month (PII), 1× per week for 6 months (PIII), and 1× per week (PIV) for 1 month.The Hamilton Rating Scale for Depression (HAM-D) (72, 73): will be applied once in PI to assess symptom severity and again 3× per week for 1 month (PII), 1× per week for 6 months (PIII), and 1× per week (PIV) for 1 month.Vital signs (VS): pulse oximetry, heart monitoring, breathing rate, heart rate, and blood pressure will be checked continuously using non-invasive methods. VS to be monitored 3× per week for the 1st month (PII) and 1× week (PIII) for 2 h continuously after completion of each application.Global Clinical Impression (GCI) scale: this will be applied 3× a week for 1 month (PII), 1× week for 6 months (PIII), and 1× week (PIV) to assess disease severity, global improvement of the condition and hence, treatment efficacy (74).Depression Thoughts Scale (DTS): the DTS will be applied at visit one (V-1), V11, and V-39 to assess for thought distortions (75, 76).Clinician-Administered Dissociative States Scale (CADSS): this will provide a measure of the dissociative effects of ketamine and will be applied 3× per week for the 1st month (PII), and 1× per week for 6 months (PIII), ~1 h after application of injections (77).Young's Mania Rating Scale (YMRS): this scale will be employed in this study to assess manic switching as an adverse effect of the medications and applied 3× week for the 1st month (PII) and 1× week for 6 months (PIII), ~1 h after application of injections (78).Brief Psychiatric Rating Scale (BPRS): Sub-item 12 of the scale will be used for detecting the presence of psychotic symptoms arising after application of ketamine, applied 3× week for 1 month (PII) and 1× week (PIII), ~1 h after application of injections (79).Udvalg Kliniske Undersoegelser Side Effect Rating Scale (UKU-SERS): this will be used to determine the presence of side effects of the medications used and will be applied 3× week for the 1st month (PII) and 1× week (PIII) thereafter, around 1 h after application of injections (79).World Health Organization Quality of Life, brief version (WHOQOL-Bref): this scale will be applied at V-1, V-11, and V-35 (80).Sheehan Disability Scale (SDS): this scale will be applied at V-1, V-11, and V-35 (81).

**Table 1 T1:** Outcome measurements over time.

**Scales**	**Baseline**	**P1**	**End of P1**	**P2**	**End of P2**	**P3**	**P4**
SCID	x						
MADRS		x		x		x	x
HAM-D	x	x		x		x	x
CGI-S	x	x		x		x	x
DTS	x		x		x		
Physical and neurological exams	x						
Clinical tests and ECG	x						
VS		x		x		x	
UKU-SERS		x		x		x	
BPRS-12		x		x		x	
CADSS		x		x		x	
YOUNG		x		x		x	
WHOQOL-Bref							
SDS	x		x		x		x
Neuropsychological assessment	x				x		

SCID, Structured Clinical Interview for DSM Disorders; MADRS, Montgomery–Åsberg Depression Rating Scale; HAM-D, Hamilton Depression Scale; CGI-S, Clinical Global Impression—Severity; DTS, Depressed Thoughts Scale; VS, Vital Signs; UKU-SERS, Udvalg for Kliniske Undersøgelser Side Effect Rating Scale; BPRS-12, Brief Psychiatric Rating Scale; CADSS, Clinician-Administered Dissociative States Scale; YOUNG, Young Mania Rating Scale; WHOQOL, World Health Organization Quality-of-Life scale; SDS, Sheehan Disability Scale.

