The safety of ketamine has been confirmed for some decades, with anesthetic doses of 4–5 mg/kg intramuscularly (IM) proving effective [93–100% of children (1,022 pediatric cases)] for airways, emesis, or agitation (46). In a small number of patients, the drug can temporarily affect heart rate, and blood pressure and promote myocardial ischemia, although these risks can be attenuated by the use of sub-anesthetic doses and careful patient selection (27, 41, 44, 47). Dissociative states, a common side effect of the drug, are transient (lasting ~40 min, 2 h after use) and are not associated with persistent psychosis or mood swings (48). Of 158 patients given ketamine, 21 (13.3%) withdrew from the study, compared to 10 (7.4%) out of the 135 patients receiving control interventions (OR 1.95, 95%CI 0.86–4.42, *z* = 1.59, *p* = 0.11) (39). Claims that NMDA receptor blocking can cause “brain damage” and that ketamine affects the urinary retract remain the subject of controversy (49). The most common (≥20%) adverse events following the use of the drug include, headache, anxiety, dissociation, nausea, dizziness, and drowsiness on days of the administration, with these effects dissipating within 2 h, while more serious side effects leading to hospitalization or suicide attempts are rare (40, 50, 51). Anti-depressant effects of ketamine are short-lived (days or weeks), although longer-term benefits can be maintained by use of repeat doses, warranting further studies on the prolonged effects of the drug (44, 52). Intranasal (IN) esketamine was approved for use in 2019 by both the U.S. Food and Drug Administration (FDA) and the European Medicines Agency (EMA) (53). Other administration routes have also been investigated: IN, subcutaneous (SC), and oral (54–56).

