### Inclusion and exclusion criteria

**The following individuals will be eligible for study inclusion:** Subjects residing in Itajaí valley (Santa Catarina state, Brazil); adults (age 18–40 years) with a primary diagnosis of TRD based on clinical evaluation and confirmed by the SCID-IV [research version (TRD defined as failure of 2–5 clinical trials with anti-depressants including ECT)]; moderate-severe intensity disease [clinical criteria and/or score ≥14 on the Hamilton Depression Rating Scale (17-item HAM-D)]; with no psychotic symptoms; not presenting an imminent risk of suicide (as indicated by clinical evaluation and HAM-D) and/or murder; with anxiety disorders (secondary); with compensated clinical comorbidities and; literate and able to understand the tasks requested (69). Patients and/or legal guardians must be aware of the nature of the study and give consent by signing the Free and Informed Consent form. All patients will undergo a physical and neurological examination, laboratory tests, and an electrocardiogram (ECG) to ascertain their comorbid clinical and/or uncompensated conditions. **The following individuals will be excluded from the study:** Subjects exhibiting imminent risk of suicide, presenting bipolar spectrum disorders or other diagnosed psychiatric conditions (primary); psychoactive substance dependence within the last year; intellectual deficit; allergy to ketamine; and glaucoma. Fertile women must be in use of a clinically acceptable method of birth control [oral contraceptive and/or condom (only unfollowed topic in GCP)]. In the event of clinical doubt regarding pregnancy, a test for beta-human chorionic gonadotropin (βHCG) hormone will be ordered. Patients who become pregnant during the study period will be excluded and referred for obstetric care. The medication wash-out period required before visit 0 will be 1 week for antipsychotics, antidepressants [except fluoxetine (4 weeks)], and for mood stabilizers. No other medications with psychiatric action will be allowed during the study, except for Lorazepam and Zolpidem for patients in the use of a benzodiazepine or hypnotic agent.

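### As written, the side-effect, dissociation, mania and psychosis scales have no clear rating before the first injection, so side-effect rates and change from v-0 lack an untreated reference

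*Protocol article*

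**What the plan says.** Measures and outcome variables gives each scale its own schedule. UKU-SERS is applied "3× week for the 1st month (PII) and 1× week (PIII) thereafter, around 1 h after application of injections", and its purpose is worded as "this will be used to determine the presence of side effects of the medications used". CADSS, YMRS and BPRS sub-item 12 follow the same pattern: PII and PIII only, about 1 h after injection. Their purposes are also framed as drug effects. The BPRS item, for instance, serves for "detecting the presence of psychotic symptoms arising after application of ketamine, applied 3× week for 1 month (PII) and 1× week (PIII"). None of the four is given a rating in PI, the pre-treatment phase, whereas HAM-D in the same list is.

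Table 1 ("Outcome measurements over time") leaves the Baseline cell empty for all four scales and marks P1, P2 and P3. HAM-D, CGI-S, DTS and SDS do have a Baseline mark.

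Statistical analysis applies a two-way repeated-measures ANOVA to the main outcome and the other scales, from v-0 to the final visit. Study hypotheses lists safety and tolerability of IM ketamine as objectives.

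**The concern.** A rating taken only after dosing shows that a symptom is present, not that it is new. The entry criteria make standing complaints likely. Patients "with anxiety disorders (secondary") are admitted, lorazepam and zolpidem are allowed for patients already using such drugs, and most psychotropics may be stopped as little as one week before visit 0. The Introduction's own list of the most common ketamine events reads "headache, anxiety, dissociation, nausea, dizziness, and drowsiness on days of the administration". A patient who enters with anxiety, headache or drowsiness can therefore register a side effect at the first rating, whatever the treatment.

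Two results are exposed: the within-arm side-effect rates, on which the tolerability objective rests, and the visit effect from v-0, if v-0 is itself a post-injection reading. An analysis plan can define a treatment-emergent event, but it cannot supply a rating that was never taken.

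**Working it through.** **1. Where v-0 falls.** Inputs come from Design and study populations and from Intervention.
- Acute phase: 3 per week × 4 weeks = 12 injections, as the article states.
- Maintenance: 1 per week × 24 weeks = 24 injections, as the article states.
- Post-treatment: 4 weekly visits.
- Total: 12 + 24 + 4 = 40 visits, which numbered from zero run v-0 to v-39.

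The last acute visit is then v-11, the last maintenance visit v-35 and the last post-treatment visit v-39. These are the numbers the article attaches to DTS, WHOQOL-Bref and SDS (V11, V-35, V-39). So v-0 is most likely the first injection visit, and the v-0 value of the four scales is a reading about 1 h after the first injection.

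One detail does not fit. The text puts DTS and SDS at V-1 (for DTS, called visit one), and Table 1 marks both under Baseline. If v-0 is the first injection, V-1 is the second, which is not a baseline. The numbering therefore points to v-0 as an injection visit but does not prove it.

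**2. What P1 means in Table 1.** Two readings are possible.
- *P1 is PI (pre-treatment).* The labels agree, and the blank P4 cells agree with the text, which gives the four scales no PIV rating. But PI has no injections, so a rating timed 1 h after one cannot occur there. HAM-D, rated once in PI by the text, would also be marked twice before treatment (Baseline and P1).
- *P1 is the acute phase.* DTS at V11 falls under End of P1, SDS at V-35 fits End of P2, and the neuropsychological tests at the end of PIII fall under End of P2. But P3 would then be post-treatment, where the text schedules none of the four scales, and P4 would have no phase.

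Neither reading fits the whole table. The second agrees better with the injection-based timing, so P1 most likely means the acute phase.

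**3. Effect on side-effect rates.** The article gives no entry prevalence and no expected event rates, so all inputs here are assumed. Let p be the proportion with the symptom at entry, the same in both arms, and q the rate of new symptoms among the rest. If presence alone is counted:

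counted rate = p + (1 − p) × q

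difference between arms = (1 − p) × (q for ketamine − q for control)

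With q = 30% for ketamine and 10% for control, a difference of 20 points:

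| Entry prevalence p | Ketamine counted | Control counted | Difference |
|---|---|---|---|
| 10% | 0.10 + 0.90 × 0.30 = 37% | 0.10 + 0.90 × 0.10 = 19% | 18 points |
| 20% | 44% | 28% | 16 points |
| 30% | 51% | 37% | 14 points |
| 50% | 65% | 55% | 10 points |

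Both rates rise and the difference shrinks by the factor (1 − p). If the two values of q are equal, the difference is zero for every p, so no false difference is created on average.

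**The case against.** Five points can be made for the plan.

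- **Table 1 may schedule a pre-treatment rating.** By the article's own phase names, a mark under P1 could mean PI. This stands as an ambiguity, so a reader should not infer that the trial certainly takes no such rating. The injection-based timing in the text still makes the other reading more likely.
- **No attribution rule is stated.** A reader might infer that entry symptoms will be scored as drug effects. The article does not say so, and a treatment-emergent definition may sit in the full protocol or analysis plan. What the article supports is that they can be counted, because no earlier value is clearly scheduled for comparison.
- **The four scales differ.** Psychotic symptoms and bipolar spectrum disorders are excluded at entry, so it would be too strong to say that new mania or psychosis could not be recognised. That reference is clinical rather than a score, but it weakens the point for YMRS and BPRS sub-item 12.
- **Randomisation protects the comparison.** Entry symptoms are equal in expectation across arms, and chance imbalance is already reflected in the standard error. Adjusting for an entry rating would gain precision, not remove bias. This stands. It does not rescue the within-arm rates or the change from v-0, and over most of the trial the control arm is itself on escitalopram and aripiprazole.
- **Entry anxiety is not the same as drug-related anxiety.** The Introduction describes the listed events as arising on administration days and passing within 2 h. That is fair, but a single rating 1 h after injection cannot separate the two, nor does it show how long an entry complaint lasts into treatment.

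**Conclusion.** The point holds in a limited form. On the schedule in the text, the four scales are rated only after injections, and v-0 is most likely the first of these readings, so change from v-0 on them has no untreated reference. The consequence is side-effect rates that can be too high in both arms and a diluted contrast. The point is strongest for UKU-SERS, plausible for CADSS, and weaker for YMRS and BPRS sub-item 12.

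A reader might infer a bias that makes ketamine look worse than control. The documents do not support this: with concurrent 1:1 randomisation no systematic false ketamine effect arises.

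The dilution from 20 points to between 18 and 10 rests on assumed new-symptom rates of 30% and 10%, an assumed entry prevalence of 10–50%, and counting by presence alone. It shows direction and scale, not an estimate for this trial. The conclusion also rests on reading P1 as the acute phase and v-0 as the first injection visit. Both are the more likely readings, and neither is certain.

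**What to change.** Rate UKU-SERS, CADSS, YMRS and BPRS sub-item 12 once after wash-out and before the first injection, at a visit that already exists (end of PI, or v-0 before dosing). If only one scale can be added, it should be UKU-SERS. Mark the rating in Table 1, relabel its columns to match PI–PIV, and state which visits v-0 and V-1 are. Report side effects as increases over the pre-injection rating, and use that rating as a covariate in the arm comparison of the continuous scores. If such a rating is already taken, correcting the text and table is enough.

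The cost is one extra administration per patient of scales already in use. The rating cannot be recovered after the first injection, and the article says the study is running. Patients already enrolled will lack it and should be reported as such.
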